## Abstract

**Background:**

Up to 27% of the German population suffers from recurrent or persistent pain (lasting more than 3 months). Therefore, prevention of chronic pain is one major object of pain management interventions. The aim of this nationwide, multicentre, randomised controlled trial is to evaluate the efficacy of a 10-week ambulatory (outpatient) interdisciplinary multimodal pain therapy (A-IMPT) for patients with recurrent pain and at risk of developing chronic pain. This project was initiated by the German Pain Society (Deutsche Schmerzgesellschaft e.V.) and the public health insurance provider BARMER. It is currently funded by the German Innovation Fund (01NVF20023). The study PAIN2.0 focuses on reducing pain intensity and pain-related disability and investigates whether this intervention can improve physical activity, psychological well-being, and health literacy.

**Methods:**

PAIN2.0 is designed as a multicentre 1:1 randomised controlled trial with two parallel groups (randomisation at the patient level, planned *N* = 1029, duration of study participation 12 months, implemented by 22 health care facilities nationwide). After 6 months, patients within the control group also receive the intervention. The primary outcomes are pain intensity and pain-related impairment, measured as Characteristic Pain Intensity (PI) and Disability Score (DS) (Von Korff) (baseline to 6 months follow-up). Secondary outcomes are the number of sick leave days, sickness allowance, treatment costs, psychological distress, health-related quality of life, catastrophising, and patient-related satisfaction with the intervention. The effects of the intervention will be analysed by a parallel-group comparison between the intervention and control groups. In addition, the long-term effects within the intervention group will be observed and a pre-post comparison of the control group before and after the intervention will be performed.

**Discussion:**

Recurrent or persistent pain is common in the German population and causes high costs for patients and society. The A-IMPT aims to improve pain and pain-related impairments in pain patients at risk of chronification, thereby reducing the risk of developing chronic pain with its high socioeconomic burden. This new therapy could easily be integrated into existing therapy programs if positively evaluated.

Trial registration

The trial PAIN2.0 has been registered in the German Clinical Trials Register (DRKS) since 21/11/2022 with the ID DRKS00030773 [https://drks.de/search/de/trial/DRKS00030773].

This publication provides an update to the original study protocol, which was first published on 23 February 2024 [https://doi.org/10.1186/s13063-024-07975-4, BMC Trials]. Due to recruitment problems during the course of the project, the originally planned number of cases could not be achieved. In order to be able to provide sufficient information about the primary effects of the study, the number of primary endpoints was reduced from 3 to 2. The primary analysis period is now 6 months without including an additional measurement point after 3 months.

## Introduction

### Background and rationale {6a}

‘Prevention of chronic pain’ was the theme of the International Association for the Study of Pain’s conference Global Year 2020 (IASP’s Global Year) [1]. However, activities to develop, evaluate and improve diagnostic and treatment options for prevention are still rare. Given the overall burden of chronic pain on individuals and society [2–4], the goal of preventing recurrent pain from becoming chronic should be a high priority for researchers, clinicians, and policy makers.

According to a nationwide survey of German citizens, approximately 27% experience recurrent pain in various locations, 7% experience recurrent pain with functional and somatic limitations, and 3% report recurrent pain with biological and psychosocial limitations [5]. These findings are consistent with other European studies [4].

Currently available diagnostic and treatment options commonly focus on the treatment and management of chronic pain. However, health care delivery for individuals transitioning from acute to chronic pain is often characterised by overtreatment with medications, invasive treatments (e.g. surgery) and imaging diagnostics, accompanied by undertreatment in the form of early psychosocial and interdisciplinary diagnostics and interventions [6]. These established approaches thus lead to iatrogenic effects (risk factors caused by the health care system, e.g. misinformed care givers or unimodal treatment approaches), enhancing the development of chronic pain forms in general [7]. Preventing individuals from developing impairing chronic pain conditions not only alleviates the burden on those affected but also helps save limited social and economic resources.

The perspective of prevention regarding pain management comprises three different stages [8]. Primary prevention focuses on identifying and improving maladaptive and non-functional workplaces and lifestyle habits that contribute to the occurrence of pain resulting from the over- or disuse of the body. Secondary prevention aims to maintain or improve physical and/or psychosocial functioning despite recurrent pain while preventing the development of chronic pain conditions. Tertiary prevention addresses individuals with chronic pain, thus reducing the risk of work disability, impaired social participation and the increase of psychological consequences such as depression, anxiety or loneliness. All approaches targeting pain and its management require the involvement of a multidisciplinary team in an integrated approach, ensuring the acknowledgement of the biopsychosocial nature of any kind of pain experience.

The biopsychosocial understanding of pain (either acute or chronic) [9] demands corresponding approaches covering biopsychosocial mechanisms of causing or maintaining recurrent pain experience. Biopsychosocial health care delivery (syn. also interdisciplinary, integrative pain care) includes complex interventions (multimodal), provided by a multidisciplinary team within an integrated team approach (interdisciplinary pain treatment, see IASP Homepage [10]). Key characteristics are equally contributed information and an integrated alignment on diagnoses and treatment components based on a shared understanding of the individual pain model of the patients using the same language and philosophy.

While biopsychosocial approaches have a well-established history in the treatment and management of chronic pain [11], their development in the context of prevention has been somewhat inconsistent.

Consequently, a concept of interdisciplinary group therapy was developed, piloted and adapted as outlined by Kaiser et al. in 2020 [12]. The intervention’s concept, which falls under the category of secondary prevention, draws from existing evidence regarding individuals with recurrent pain and those at risk of developing chronic pain.

The overall aim of PAIN2.0 is to improve the care of patients undergoing the transition from acute to chronic pain in an outpatient setting. The study involves the implementation of an ambulatory (outpatient) interdisciplinary multimodal pain therapy (A-IMPT) for individuals with persistent or recurrent pain, who, at the time of indication, have risk factors for the development of chronic pain and an increased physical and/or psychosocial disability.

#### PAIN2.0

PAIN2.0 is a consortium project of the Innovation Fund (01NVF20023) with a duration of 42 months.

The consortium leader is the German Pain Society (Deutsche Schmerzgesellschaft e.V.). The consortium partners involved in the project management (PM) are a public health insurance provider (BARMER), an external evaluation institute (Institute for Community Medicine, University Medicine Greifswald), as well as four institutions with profound experience in delivering interdisciplinary multimodal pain therapy (IMPT) (German Red Cross Pain Centre Mainz, University Hospital Carl Gustav Carus Dresden, University Hospital Schleswig-Holstein/Lübeck, University Medical Centre Göttingen).

#### Objectives {7}

The main objective of the project is to improve health care delivery for patients suffering from recurrent pain and present risk factors for chronification. Therefore, a therapy adapted to the needs of outpatients with pain is developed. The therapy entails delivering early information on the characteristics of pain, possible risks of chronicity, and the early identification of strategies to mitigate mechanisms that lead to chronicity. The transfer of a biopsychosocial understanding of the disease and specific knowledge about individual and contextual risk factors influences pain onset, equipping patients to develop adaptive coping strategies. The ultimate goal is to empower patients to take an active role in managing their pain. The following objectives for an outpatient interdisciplinary multimodal pain therapy are derived:Enhancing the sense of control and self-efficacyTeaching self-responsibility and building competence in the use of pain reduction techniquesIntroducing a biopsychosocial modelProviding education about the specificity of painOffering information on psychosocial risk factors

Therefore, the A-IMPT aims to (1) improve the objective and subjective performance as well as the subjective ability to control (physical activity and performance, health literacy, flexible self-regulation) and (2) prevent the development of chronic pain, especially in terms of pain intensity and pain-related impairment, compared to standard care.

The working hypotheses are:Over a 6-month period, participants in the intervention group are expected to report lower pain intensity than those in the control-group.Over a 6-month period, participants in the intervention group are expected to report less pain-related functional disability than those in the control-group.

#### Trial design {8}

The study is designed as a nationwide, multicentre randomised controlled trial (RCT), with two parallel groups to evaluate the efficacy of a 10-week outpatient interdisciplinary multimodal pain therapy. The duration of study participation is 12 months. Patients are enrolled consecutively from January 2023 to February 2024. Following verification of inclusion and exclusion criteria, they will be allocated to either the intervention group or the control group in a 1:1 ratio. The intervention is scheduled to occur between March 2023 and November 2024. Control group patients will receive standard care for 6 months, with the option to participate in the intervention program subsequently. Please refer to Fig. 1 for an overview of the study’s procedural timeline.

**Fig. 1 Fig1:**
[figure not shown]
Timeline and analysis approach

Intervention effects will be analysed as follows:Essentially, the intervention effect will be evaluated by analysing the course of the primary and secondary outcomes in the intervention and control groups within the first 6 months (parallel-group comparison, *t*_0_ to *t*_2_) (Fig. 1b).In a secondary analysis approach, the long-term course of the new intervention is examined (*t*_2_ to *t*_4_). Further analyses of the outcome variables at these points are important for evaluating the stability of this effect over time (long-term) (Fig. 1c).The control group receives the intervention in the second half of the study period. The course of the primary and secondary outcomes in the control group after starting the intervention (*t*_0_ to *t*_2_ vs. *t*_2_ to *t*_4_) will be analysed (Fig. 1d). From a methodological perspective, this pre-post comparison can also help mitigating selection biases by increasing the willingness to participate in the study and reducing the drop-out rate within the control group.

The centres play a crucial role in the implementation of the new intervention, undertaking vital responsibilities in patient recruitment (including patient information and securing informed consent), overseeing and documenting study-related procedures, collecting data, and transmitting data sets. Each centre receives comprehensive training on study protocols and tasks, both study-related and intervention-related. They actively participate in (online) project meetings and profession-specific intervision and undergo thorough monitoring. Additionally, these centres contribute to regional recruitment efforts, providing support and outreach within their respective areas.

### Eligibility criteria {10}

*Primary* criteria for study inclusion comprise the following:New onset of pain (at least 6 weeks ago) or recurrent forms of pain or pain persisting for a longer periodPain-related limitations relevant to the patient (e.g. previous sick leave days, interference with daily life, family, leisure, work, and homework) and associated with reduced quality of lifeA risk of developing chronic pain (e.g. pain spread, negative mood, family and work stress factors, avoidance, and avoidance behaviour)

Patients must be at least 18 years old, have sufficient knowledge of the German language in spoken and written form, live in the vicinity of the participating health care facility, and have given their verbal and written consent to participate.

*Primary* criteria for study exclusion comprise the following:Clinical signs of a serious illness requiring urgent acute therapy or other serious illnesses (red flags; e.g. severe cardiac insufficiency, tumour)A manifest chronic pain condition that has already occurred (e.g. sick leave due to pain for more than 6 months, previous treatment with strong opioids for more than 3 years, previous IMPT)A severe and active psychiatric disorder (personality disorder, severe depression, signs of suicidal tendencies)An ongoing application for retirementA rehabilitation procedure planned for the near futureLinguistic and/or cognitive impairments

The primary inclusion and exclusion criteria refer to the target population of PAIN2.0. However, there are additional *secondary* inclusion and exclusion criteria that are relevant for group participation and once again describe a subpopulation from the overall target population for inclusion in the PAIN2.0 group programme.

In addition to the general requirement of being able to participate in a 10-week group therapy and residing in close proximity to the facility, profession-specific secondary exclusion criteria were established. These secondary exclusion criteria included medical, physiotherapeutic, and psychological indicators that would limit regular participation in the therapy program and the benefits thereof. They are as follows:

Medical:Limited physical function for A-IMPT from a medical point of view, health check (check of exclusion criteria, medical)Presence of concomitant diseases that require special monitoring or limit the resilience for the A-IMPTNeed for withdrawal treatment that requires continuous monitoringExisting drug dependence (e.g. opioids, benzodiazepines)Presence of an acute pain exacerbation that makes participation in the A-IMPT impossible

Psychological:Restricted psychological functionRestricted social resources in terms of supporting constant group attendancePresence of a manifest, severe psychiatric/psychological diagnosis that primarily indicates psychotherapy (e.g. severe depression, personality disorder)Limited group capacityRestricted motivation to participate regularly

Physiotherapy:Limited self-care (i.e. daily physical activities, in the sense of managing personal affairs, personal hygiene and mobility)Limited mobility for participation in the A-IMPTLimited physical capacitiesPronounced movement-related fear-avoidance behaviourRestricted movement-related competenciesIndication for IMPT with higher intensity (‘more’ than A-IMPT)Need for priority, specific physiotherapy treatment.

### Who will take informed consent? {26a}

Informed consent is obtained by the responsible physicians in the centres. They provide comprehensive information about the study and its schedules.

Before asking for consent, the procedure of inclusion contains two steps: primary inclusion criteria will be evaluated by the responsible physician and cover eligibility criteria as described above. Secondary inclusion criteria will be evaluated by the team (physician, physiotherapy and psychology). After fulfilling primary and secondary criteria, patients will be asked to give consent and will be consecutively included in the study.

### Additional consent provisions for collection and use of participant data and biological specimens {26b}

N/a. There are no additional consent provisions.

### Interventions

#### Explanation for the choice of comparators {6b}

The comparator is the standard healthcare as currently applied in the standard pain therapy in Germany. Patients in the intervention group will receive the new intervention at the beginning of the first 6 months, whereas participants in the control group will not receive any trial-related healthcare interventions. However, they are permitted to continue their pre-existing medical, physiotherapeutic and/or psychological (pain-related) therapies, which is often referred to as ‘treatment as usual’.

The comparator was chosen to identify the effects of the new intervention and to improve the currently applied pain therapy. Therefore, a comparison to ‘usual care’ is eligible. It is worth noting that patients in the control group also receive interventions after the initial 6 months (Fig. 2; see also Fig. 1).

**Fig. 2 Fig2:**
[figure not shown]
Flow chart of participants

### Intervention description {11a}

Interdisciplinary multimodal pain therapy [15] is commonly applied in chronic pain treatment. It is described as an integrative therapy approach consisting of somatic, psychotherapeutic, and physiotherapeutic interventions. Physicians, physiotherapists and psychologists collaborate equally in an integrative team approach and regularly coordinate and align on diagnosis, treatment plan and treatment progress. The primary goal of treating chronic pain by IMPT is to restore the patient’s subjective and objective functioning and self-control.

In this project, the IMPT is applied to an outpatient setting (A-IMPT) and adapted to the aims for the above-described target population.

The A-IMPT takes place once a week for 3 h in 10 sessions over 12 weeks in groups of 10 patients. It consists of 5 modules in total, each thematically grouped (Fig. 3). There are two sessions within each module, led by the respective professions. Throughout the 10 sessions, psychologists and physiotherapists are each present for a total of 30 h, while the presence of the physicians in the group sums up to 15 h. It is important to note that the content within each module is taught collaboratively by one or more professions.

**Fig. 3 Fig3:**
[figure not shown]
Treatment plan and components of the A-IMPT

In the beginning, the general focus is on knowledge transfer, which is progressively expanded through practical exercises and integrated into the patient's background of experience (deepening of problem actualisation and enhancing motivational clarification). Therapeutic interventions (resource activation, problem-solving) are introduced from the beginning to support the transfer into everyday life. Each session ends with practical content (exercises, discussion, task to take home), which is taken up in the following week's session and leads into the new topic. In this way, patients experience health literacy to maintain a healthy, physically active lifestyle.

In addition to group therapy, all therapists also have the flexibility to offer 30 min of one-on-one time to each patient throughout the 10 weeks. Regular interdisciplinary team meetings are scheduled every 2 weeks to discuss each patient, lasting 30 to 60 min. A final meeting including the patient and all of the involved healthcare professionals of about 15 to 20 min completes the treatment. It serves to summarise the patient’s experiences, diagnoses, and further recommendations. As a conclusion, a collective final letter is written.

Coordination of group appointments, cancellations and provision of materials is handled by the documentation assistant or the nursing staff.

### Criteria for discontinuing or modifying allocated interventions {11b}

Discontinuation of the study at the participants’ request is possible at any time during participation in treatment or the waiting period without giving reasons.

During participation and waiting period, patients continue to have full access to the health care system (i.e. primary care physicians or specialists). Changes in the participants’ medical treatment are assessed during the individual one-on-one contact with the physician as part of the A-IMPT. In the delayed treatment period of the control group, medical changes will be additionally assessed at the face-to-face interim contact (30 min) 3 months after study inclusion.

Reasons for study discontinuation also include any medical conditions that impact the participant’s ability to continue participating in the A-IMPT, whether they are related to pain or unrelated medical circumstances (e.g. need for urgent surgery or hospitalisation). Exacerbation of pain requiring intensified pain management (inpatient treatment/hospitalisation) will result in study discontinuation. However, discontinuation is not necessary if the pain exacerbation or new-onset pain can be adequately treated (including surgical intervention or short-term opioid prescription, if necessary) without compromising the ability to participate in the intervention (A-IMPT). Furthermore, physiotherapeutic and psychological reasons for study discontinuation are documented during the biweekly team meetings. The decision to discontinue the study is always made collaboratively by the treatment team.

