### Strategies to improve adherence to interventions {11c}

Before the start of recruitment, the centres receive training in the interventions, study documentation and data management, utilisation of assessment instruments, transmission of study documentation to the evaluating institutions, as well as the procedures and obligations regarding data validation. Training is mandatory; furthermore, written and video-based training materials are accessible through an access-restricted website.

A comprehensive monitoring concept has been developed and will be executed by the project administration (Deutsche Schmerzgesellschaft e.V.) in collaboration with consortium partners, including the German Red Cross Pain Centre Mainz, University Hospital Carl Gustav Carus Dresden, University Hospital Schleswig-Holstein/Lübeck, University Medical Centre Göttingen, and the evaluating institution (University Medicine Greifswald). The monitoring aims to oversee the implementation and adherence to the study protocol, provide direct feedback to the centres, and document any relevant deviations. It commences immediately after the recruitment and inclusion of the first patients.

For participants of the control group, an intermediate medical visit (interim contact) is scheduled after 3 months to prevent dropout. In addition to reassessing the status of the inclusion and exclusion criteria, a brief status report on the patient’s condition is given, and the patients should be motivated to attend the later intervention.

The principle of data management and monitoring has been described in a comprehensive data management plan.

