## Assignment of interventions: blinding

### Who will be blinded {17a}

N/a. Blinding is not possible.

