### Methods in analysis to handle protocol non-adherence and any statistical methods to handle missing data {20c}

In longitudinal analyses involving more than one follow-up time point, the family of (generalised) mixed models uses all available data, even if data at some time points are missing. If necessary (e.g. in case of high drop-out-rates > 30%), appropriate methods of (multiple) imputation of missing values will be employed. The population for primary analysis includes all patients for whom PI and DS data are available at baseline and at 6-months-follow-up.

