### Adverse event reporting and harms {22}

N/a. The occurrence of adverse events is not expected in this trial.

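### Study discontinuation for worsening pain, with a completer primary population and no harms comparison, lets the patients who worsen most drop out of the primary analysis

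*Protocol article*

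**What the plan says.** Six sections of the protocol article bear on this point.

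- **Criteria for discontinuing or modifying allocated interventions {11b}**: "Exacerbation of pain requiring intensified pain management (inpatient treatment/hospitalisation) will result in study discontinuation". Medical conditions that affect the ability to continue A-IMPT, such as urgent surgery or hospitalisation, are also reasons for study discontinuation. An exacerbation that can be treated adequately without compromising participation is not. On who decides: "The decision to discontinue the study is always made collaboratively by the treatment team". For the group therapy, "physiotherapeutic and psychological reasons for study discontinuation are documented during the biweekly team meetings".
- **Strategies to improve adherence {11c}**: "For participants of the control group, an intermediate medical visit (interim contact) is scheduled after 3 months to prevent dropout". The content of that visit begins: "In addition to reassessing the status of the inclusion and exclusion criteria". No consequence of failing a criterion is given, and no matching re-check is described for the intervention arm.
- **Plans to promote participant retention and complete follow-up {18b}**: reasons for discontinuation are documented, and a list of outcome data is to be compiled for participants who discontinue or deviate.
- **Statistical methods {20a}**: the primary endpoints are to be analysed by intention to treat, with the 6-month value as outcome and baseline and group as predictors.
- **Missing data {20c}**: "The population for primary analysis includes all patients for whom PI and DS data are available at baseline and at 6-months-follow-up". Multiple imputation is used only if necessary, with drop-out above 30% as the example.
- **Adverse event reporting and harms {22}**: marked not applicable, because "The occurrence of adverse events is not expected in this trial".

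On blinding {17a}: "Blinding is not possible".

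**The concern.** The primary outcomes are pain intensity and pain-related disability. A rule that ends study participation because pain has become bad enough for inpatient care selects on the outcome itself. If the same patients then have no 6-month value, the completer population leaves them out, and each arm is judged on those who did not deteriorate that far.

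This would matter less if the loss were sure to be equal in both arms. The trial is unblinded, the treatment team takes the decision, and the arms are watched differently. Patients in A-IMPT are discussed every two weeks and see the physician individually. Controls have one scheduled contact at 3 months, at which eligibility is checked again. Unequal detection can produce unequal loss, and the treatment contrast then carries a bias that randomisation does not remove.

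The harms section gives no second view. It plans no reporting, while {11b} itself anticipates hospitalisation, urgent surgery and exacerbation. An imbalance between arms in such events would have no planned place in the results.

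**Working it through.** **1. Do the analysis rules recover a discontinued patient?**

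| Possible route back into the analysis | What the protocol gives |
|---|---|
| Intention to treat {20a} | Declared, but the population in {20c} requires PI and DS at 6 months |
| Mixed model using all available data {20c} | Stated for analyses with more than one follow-up; the primary model in {20a} has one |
| Multiple imputation {20c} | Conditional; example trigger above 30%, while Sample size {14} expects 20% |
| Outcome list for discontinuers {18b} | A list; no statement that 6-month PI and DS are still collected or analysed |

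At the planned drop-out, none of the four routes is sure to bring back a patient discontinued under {11b}.

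**2. How large could the effect be?** The plan has no figure of its own on this point to reproduce. Inputs from Sample size {14}: target difference 0.3 and residual variance 1.0, hence SD 1. The share p lost from an arm is not in the document, so p = 2% and 5% are assumptions.

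*Case A: those lost average 1 SD worse than the arm mean.* The remaining mean improves by p/(1−p).
- p = 2%: 0.02/0.98 = 0.020 SD, and 0.020/0.3 = 7% of the target.
- p = 5%: 0.05/0.95 = 0.053 SD, and 0.053/0.3 = 18%.

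*Case B (upper bound): those lost are exactly the worst tail of a normal outcome.* The remaining mean improves by φ(z)/(1−p), with z the (1−p) quantile.
- p = 2%: z = 2.054, 0.0484/0.98 = 0.049 SD, 16% of the target.
- p = 5%: z = 1.645, 0.1031/0.95 = 0.109 SD, 36%.

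**3. What does this do to the contrast?** The shift in the contrast is the difference between the two arms' shifts.
- Loss from controls only makes controls look better and counts against A-IMPT.
- Loss from the intervention arm only counts in favour of A-IMPT.
- Equal loss roughly cancels.
- Under Case B with 5% in one arm and 2% in the other, the net shift is 0.1086 − 0.0494 = 0.059 SD.
- If discontinued patients stay in 6-month follow-up and analysis, this bias is zero.

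**The case against.** The best defence is that {11b} is headed as a section on discontinuing interventions, ties its medical criterion to the ability to take part in A-IMPT, and may use study discontinuation loosely. The retention section provides for outcome data on discontinuers, and the full protocol and data management plan are not shown. This stands in part: the article does not prove that 6-month questionnaires stop. But its wording concerns the study, and its population definition admits only patients with 6-month data. If continued follow-up is intended, these sections misstate it.

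Some stronger readings are tempting and are not supported.

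- A reader might infer that controls who fail the 3-month re-check are removed. {11c} states no consequence, and gives the visit's purpose as preventing drop-out and motivating patients for the later intervention.
- A reader might infer that only controls are scrutinised. The intervention arm is also assessed, at the biweekly meetings and the physician contact. The monitoring is different, not one-sided.
- A reader might infer that worsening under A-IMPT would be invisible. Exacerbations that can be managed without stopping participation stay in the primary outcome. Discontinuation reasons are documented, and inpatient costs for BARMER patients are a secondary outcome from insurance data. What is missing is a planned comparison by arm.
- The tail-loss figures could be read as an expected bias. They are an upper bound that assumes loss of the exact tail from one arm.

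**Conclusion.** The concern holds in a limited form. Read as written, the discontinuation rule, the completer population and the conditional imputation together allow patients who worsen most to leave the primary analysis, which is inconsistent with the declared intention-to-treat principle. Differing monitoring in an unblinded trial makes unequal loss possible. The documents fix neither its size nor its direction.

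On the assumption of 2–5% lost from one arm, the shift is 0.02–0.05 SD if those lost average 1 SD worse and at most 0.05–0.11 SD under exact tail loss, against a target of 0.3. It is near zero if loss is balanced. That is moderate at most, but avoidable.

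On harms, marking adverse events as not applicable does not fit the events that {11b} foresees. The gap is the absence of a comparison by arm; discontinuation reasons themselves are recorded.

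**What to change.** Reconcile sections {11b}, {11c}, {18b}, {20a}, {20c} and {22}, leaving every clinical stopping rule as it is.

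1. State that stopping A-IMPT, or failing the 3-month re-check, does not end study follow-up. Such patients are still sent the t1 and t2 questionnaires and are analysed in their allocated arm unless they withdraw consent.
2. Define the primary population as all randomised patients.
3. State what the 3-month eligibility re-check is used for.
4. Replace the not-applicable entry in {22} with a table by arm of the documented discontinuation reasons, including hospitalisation, urgent surgery and pain exacerbation.

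Recruitment ended on 28/02/2024, so follow-up may already be over. In that case, retrieve any existing 6-month values for discontinued patients and report exclusions with reasons by arm.

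The cost is revised wording, a few more questionnaires and one more table. The table can cover only what was documented: the article does not say that exacerbations or operations that did not lead to discontinuation were recorded by arm.
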